**Overview:** This application is for the second, trial component of an NIMH-funded study that will build and test (with a hybrid implementation-effectiveness design) a collaborative child mental health program in Iran. The project involves investigators in the JHU SPH, University of Washington, and partners at the Tehran University of Medical Sciences (TUMS).

The overall project has been reviewed and approved by the ethics committee of the Tehran University of Medical Sciences IRB (English translation attached). Some recently-modified design elements reflected in the protocol below were submitted to and accepted by the TUMS IRB – they do not provide an updated approval. The initial formative phase of the work was approved as JHU IRB00111549. This trial phase was registered with ClinicalTrials.gov as NCT03144739 on 5/8/17.

Most mental health problems begin in childhood and adolescence, but delays in receipt of treatment are measured in years to decades (Wang 2004, 2007). As a result, mental health problems cause a disproportionate burden of disability among children and youth compared to adults, and have a major impact on life course development (Kieling 2011). Primary care services can play an important role in efforts to prevent and intervene early in the course of child and adolescent mental health problems (WHO 2003). Primary care services are widely available and offer an opportunity to interact simultaneously with children and their parents, treat mental health in the context of medical and developmental concerns, and reduce the stigma associated with visiting identifiable mental health facilities. While research with adults has shown the feasibility of integrating mental health care into primary care settings, and that it reduces the burden of mental illnesses, there have been few studies among children and youth. Evidence remains lacking that integration is feasible in diverse settings and that it improves clinical outcomes.

One essential element of integration is “shifting” first-line mental health engagement and treatment tasks to primary care providers (Patel 2013). Task shifting requires mental health interventions that fit the context of primary care services and the nature of the problems seen (Aarons 2011). To date, most adult and child integration models have targeted single conditions at diagnostic levels and relied heavily on additional co-located personnel to provide treatment. However, to achieve goals of prevention and early intervention, integration models for children and youth must take into account how the epidemiology of mental health problems in children and youth differs from that of adults. The symptoms of emerging child and youth problems often suggest multiple possible disorders and can be co-morbid with developmental and parental disorders. By definition, emerging problems amenable to early intervention are likely to be “subthreshold” and not qualify for treatment in a specialty setting, especially when resources are scarce, even though early intervention holds the promise of preventing progression (Cross 2014).

The purpose of this project is to test the effectiveness of adding a child/youth mental health component tailored to fit the context of primary care into an existing collaborative care program supporting primary care management of adult mental health problems. The rationale for carrying out the project in Iran is two-fold: first, while integration of child mental health with primary care offers opportunities to fill service gaps even in high resource countries, it is particularly important in low and middle income countries where child mental health resources are in even shorter supply and where other community-based services (such as those in schools) are also uncommon; second, Iran is typical of many countries in that it has well-developed, family-

oriented primary care and adult mental health systems but very little child mental health capacity; and third, one of the investigators has created and directs an adult mental health-primary care integration program onto which a child program can be efficiently added, allowing coordination of adult and child services at the primary care level.

### **Specific objectives**

The specific goal of this application is to conduct a hybrid effectiveness-implementation trial with general practitioners in Iran focusing on the following questions:

1. Whether delivery of the tailored interventions by primary care providers results in improved child and parent mental health outcomes; and exploring the mechanisms by which the interventions achieve those outcomes (which conditions are more likely to be identified and treated by GPs, which treatments have the greatest uptake by parents and youth).
2. Whether a coordinated program of training, ongoing coaching, and collaborative care results in uptake of the tailored intervention by primary care providers as evidenced by treatment provided in primary care and participation in collaborative care through consultation and referral.

### **Background**

Worldwide, from 10 to 20% of children and youth develop mental health problems (Kieling 2011). Neuropsychiatric problems are the leading cause of disability among young people. Because they frequently go untreated for years or decades, they create enormous burdens of disability, especially in countries with predominantly young populations (WHO 2003). However, commonly-occurring problems such as anxiety and depression can potentially be prevented or ameliorated through intervention in childhood and adolescence (Cuijpers 2005, 2008). The reviews and expert panels conducted for the WHO's Mental Health Gap Action Plan (mhGAP) supported interventions, delivered in general medical care, to detect and manage developmental disabilities, behavior problems, and depression (Patel 2013).

While school and community-based programs are also important to comprehensively approach child mental health prevention and early intervention, primary care has an important role for detection and treatment (Patel 2013). Primary care may be critical for coordination and access to services (WHO 2012). It is widely available and allows simultaneous interaction with children and their parents, treats mental health in the context of medical and developmental concerns, and reduces the stigma associated with visiting identifiable mental health facilities. However, to date, nearly all adult and child models for integration of mental health with primary care have targeted single conditions at diagnostic levels and relied on additional co-located personnel. While this has demonstrated the feasibility of integration on a limited scale, it stops short of providing a readily disseminated model for broadly addressing child mental health problems, which are often subthreshold, highly co-morbid, and can involve simultaneous treatment of parents. Countries across the spectrum of income and resources need integration models that address the range, complexity, and local idioms of child mental health problems, and that can be practically and effectively delivered by primary care providers themselves (Kieling 2011; Ventevogel 2014).

Elaborations on Wagner's Chronic Care Model (CCM) (Wagner 1996) have been the basis of most programs to integrate mental health with adult and pediatric primary care. Several CCM interventions with positive outcomes have been reported for adult depression; one positive trial has been reported for adolescent depression and one for disruptive behaviors among younger children, both using co-located personnel (Asarnow 2005, Kolko 2014). The first step in adapting the CCM for child/youth mental health involves developing the core set of engagement and self-management interventions: universal and problem-specific interventions that are

evidence-informed, suit the patients and their problems in any given community, and are feasible in general medical settings (Wissow 2008). First, the “common factors” literature from psychotherapy emphasizes how patient-provider interactions influence outcomes across diverse therapies and inform the CCM’s engagement and coaching strategies (Wissow 2011). Studies in LMICs also find that patient-provider interactions (Labhardt 2009) impact outcomes in ways similar to what is observed in higher resource countries. Second, the “common elements” of evidence-based child mental health treatments suggest interventions (Chorpita 2005) that can be matched to child and parent concerns and delivered prior to completion of a formal diagnostic process (McGarry 2008). Third, studies of “single session” psychotherapy (and other brief intervention models among adults) demonstrate the effectiveness of providing treatment in brief pulses across extended periods, similar to patterns of medical primary care (Perkins 2008). Fourth, “stepped care” models for treating adult depression suggest that generalists can provide first-contact mental health treatment if they reliably follow patients to ascertain need for further diagnosis or intervention (Katon 2010). Finally, in both mental health and medical services, effective care involves leveraging community resources to support functioning (Davis 2010). In a study in the US, we found that training community providers in “common factors” skills impacts children’s outcomes (Wissow 2008, 2011); we have preliminary evidence that this approach to integration can be successfully used for care of adults with HIV in Ethiopia (Wissow 2014; Jerene [in press]).

Tehran University Collaborative Care Program (TUCCP): In 1988, the Iranian Ministry of Health and Medical Education (MOH) set a goal of involving all rural and urban primary care centers in the detection and treatment of common and severe mental disorders. The program succeeded for adult services in rural areas (Khadiji 2012), but its reliance on community health workers (CHWs) failed in urban areas where populations were more mobile and less close-knit (Yasami 2001). In response, the MOH financed a pilot urban mental health collaborative care program, TUCCP, replacing CHWs with GPs as the first line of services and point of access to specialists (Sharifi 2011, 2014, 2015; Moinfar 2016). Led by the Iranian co-investigator of this application, TUCCP spans public and private primary care sites linking over 60 urban GPs with community mental health centers (CMHCs) for consultation, referral, and ongoing support of GP skills. For adults, the model promotes task-shifting care for common mental disorders to the GPs, and stepped care via referral for individuals with more serious mental disorders. However, for children and youth, the current model calls for GPs to function only as gateways, referring all levels of problems to a CMHC.

TUCCP is a sophisticated program that fully operationalizes the CCM and includes features advocated for US medical homes and accountable care organizations (Katon 2011). Its main components are: 1) an initial 3-day training followed by quarterly boosters and ongoing interaction between CMHCs and GPs, 2) informal mental health consultation to GPs about specific patients, including facilitating referrals to CMHCs (who may take over care or return the patient to the GP), 3) a case manager role for the GPs’ receptionists, who telephone enrolled patients to check on their status, re-enforce interventions, and remind them of appointments, 4) a health information system for ongoing case tracking and quality assurance, and 5) payment of top-up fees to the GPs (like care management fees for US certified medical homes), contingent on documented follow-up and adequate treatment. When a GP identifies a patient with a mental health problem, he/she or the receptionist enters demographic and diagnostic information and the treatment plan into the information system. A psychologist and psychiatrist from the CMHC regularly call GP offices to monitor follow-up and give feedback on treatment plans and every 3 months visit offices to audit a sample of charts and discuss management. TUCCP also regularly calls a 5% sample of enrolled patients to ask them about satisfaction with the services they have received from GPs and their receptionists.

TUCCP and child services: Presently, TUCCP focuses on collaborative care for adults. Physicians participating in the TUCCP are advised to refer identified children/youth with mental health problems to CMHCs for further care. In contrast to the volume of adults, only 192 child/youth patients were enrolled in TUCCP's first 30 months, substantially fewer than expected, and only 67% completed referral to the CMHC. TUCCP leaders attributed this under-utilization in large part to the mandatory referral of child cases to CMHCs, which constituted a disincentive for both parents and GPs. In preparation for this project, TUCCP surveyed a sample (n=27) of participating GPs to explore their interest in additional child mental health training; *78% said they would likely participate*. GPs believed that a majority of parents would welcome alternatives to referral to CMHCs. They said that parents declined CMHC referrals because of distance, stigma, and concern that specialists would propose medication rather than psychotherapy. Over 75% of patients GPs referred had conditions (ADHD and anxiety) that could be treated in primary care.

## **Study procedures**

**Design, sequence and timing of procedures:** In this phase of the work we will conduct a hybrid effectiveness-implementation trial (Curran 2012) to develop preliminary evidence of the feasibility of training GPs to address child/youth mental health problems and mechanisms leading to training uptake and outcomes. The trial is a staggered-start parallel design in which the recruited GPs will be randomly assigned to one of three groups, and then within these groups assigned to either intervention or control status. Intervention GPs will receive the child mental health training that is the subject of the study; control GPs will receive a child mental health "booster" (focusing on identification and referral) as an attention control. At the end of each group's study period the control GPs will have the opportunity to take the training received by the intervention arm. In the intervention arm, after training, if GPs believe a child/youth has a mental health problem, the GP will have the option to offer a) treatment him or herself, b) treatment in the GP office but with a referral for a one-time evaluation or c) referral to the CMHC as is currently the standard. For all cases in which the GP believes that the child/youth has a mental health problem, whether in the intervention or control group, office receptionists will register the child with the TUCCP, stay in contact with the family, re-enforce the GP's advice (whether that involves an intervention directly prescribed by the GP or involves a referral to the CMHC), and check on follow-through. All of these steps are routine parts of TUCCP care and are documented in the TUCCPs routine on-line data system.

To examine the impact of the intervention, in the first 1-2 weeks following training, cohorts of children 5-15 years old will be recruited and screened using the parent report version of the Strengths and Difficulties Questionnaire (SDQ) that corresponds to the age of their child. The SDQ has been validated in Iran and yields measures of symptoms, functioning, and family burden plus overall scores and domain scores for hyperactivity and emotional, peer relationship, and conduct problems. In studies in other countries, the SDQ has been found to have similar or better sensitivity and specificity as the much longer CBCL (Goodman 1999). Screening results will not be shared with the GP, and summary scores will not be discussed with parents. Parents and children/youth will be free to discuss the screen with the GP or anyone else, and RAs administering the screens will encourage parents to discuss any concerns they have with their GP. Those children/youth who screen positive will be followed by telephone with re-assessment at 3 and 6 months after screening (regardless of whether or not the GP has considered them to have a mental health problem and entered them in the TUCCP registry).

The following figure is the currently planned timeline for the study, assuming recruiting of GPs in February-March, 2018 and beginning the trial in March-April, 2018.

| Study year          | 2016 7       | 2017 8       | 2018 9       | 2019  |
|---------------------|--------------|--------------|--------------|-------|
| month               | JASONDJFMAMJ | JASONDJFMAMJ | JASONDJFMAMJ | JASO  |
| Formative work      | XXXXXXXXXX   |              |              |       |
| Pilot training      |              | X XX         |              |       |
| Recruit GPs         |              | X            |              |       |
| GP group 1          |              | TRFF         | FFFFW        |       |
| GP group 1          |              | CRFF         | FFFF         |       |
| GP group 2          |              | TR           | FFFFFW       |       |
| GP group 2          |              | CR           | FFFFF        |       |
| GP group 3          |              |              | TRFFFFFW     |       |
| BP group 3          |              |              | CRFFFFFF     |       |
| Crossover trainings |              |              |              | T T T |

GP=general practitioners  
 R=Recruit patients: assume that in a month with R that some will be followed for part of that month but still need six full months after  
 C=Control training  
 T=Intervention training  
 F=FINAL F/U (blue) [note that exact end date will depend on 6-month date of last-enrolled patient  
 Three month follow-up - doesn't have a letter - yellow  
 W= wrap up qualitative interviews with parents and GPs

## Population and recruiting:

**1. Children/youth and their parents:** The main participants in the trial are children/youth 5-15 years of age (male and female) and one of their parents or guardians (whoever accompanies the child/youth to their GP visit). These children will generally be coming to the GP for a non-emergent medical, emotional, or behavioral concern. Some children may have a chronic medical or mental health condition, but we will not recruit any child/youth who reports being in pain or who appears to be acutely ill. Children/youth who are actively being treated at the CMHC at the time of recruiting will also not be eligible. We plan to recruit approximately 1500 children/youth and 1500 parents (screening step) and follow about 350 of each (children who are SDQ+ and their parent) by telephone at 3 months and 6 months after the index visit.

The required patient sample size was estimated in four stages. We first used the "change" option in the "samps" routine in Stata Release 12 (StataCorp, College Station, TX 2011) to obtain a sample size disregarding clustering among general practitioners. The "change" option computes a t test on the difference in change scores (outcome minus baseline) between the intervention and control groups. The variance is adjusted for correlations between the outcome measures and between the outcome and baseline measures. We estimated that the difference in change scores at the final assessment would be about 2.5 points on the SDQ total difficulties scale, based on data from a prior trial conducted in primary care in the US (Wissow 2011) and on data from the UK child and adolescent mental health care system (Wolpert 2015). An estimated standard deviation of 7.2 was also drawn from these sources (thus an estimated effect size of .34). Correlations between baseline and outcome measures and between outcome measures were estimated at .37 and .55, respectively, also based on prior data from the US (Wissow 2011). With alpha=0.05 and power of 0.8 these parameters yielded a sample size of 135 per study arm (270 total).

In cluster-randomized studies, sample size is dependent on the extent to which outcomes are correlated within clusters. A review of adult primary care studies from high-income countries found ICC's for depression outcomes ranging from .016 to .035; the range for the SF-36 mental health measure was .009 to .033 with an overall median of 0.01 (Adams 2004). Given that we plan to enroll 45 general practitioners we would have clusters of 6 patients per general practitioner yielding a design effect of  $1+(6-1)*.01=1.05$ , or a sample size at outcome of about

284. Assuming a worst-case of 20% loss of patients to follow-up would require enrolling 355 patients.

There are varying estimates of the prevalence of high/abnormal SDQ scores ( $\geq 17$ ). We found 24% of those screened to be in this range in a study of children 6-16 in primary care in the US (Wissow 2008); Alavi and colleagues (2010) found a prevalence of 26% using this scoring of the SDQ in a population-based sample of children 6-11 in Tehran. Using an estimate of 24%, we then need to screen about 1479 children/youth.

For screening, we will recruit consecutive patients as they come for clinic visits. Families will be approached by a research assistant when they arrive for visits and asked if they are interested. Families will not be approached if the child appears to be acutely ill or in pain. If the family is interested, they will be taken to a nearby private space to discuss and consider consent/assent. We anticipate that most families will complete baseline data collection by telephone to avoid delaying their visit and to assure privacy. If time and privacy permit, consenting families will have the option to complete data collection in person before or at the end of the visit. To facilitate telephone administration, families will receive blank copies of the main questionnaires to use, if they desire, as references when later answering over the phone. Families who consent will receive a small token (value about \$2).

**2.GPs:** In this cluster-randomized clinical trial, the unit of randomization is the practice (which in most cases is the same as the GP, since most GPs are in solo practice). We will recruit from among GPs who are already taking part in the collaborative care program. These GPs are already tasked with detecting child and youth mental health problems but at present they are instructed to refer all such children to the CMHC. GPs will be randomized in a way that balances, to the extent possible, characteristics of their practice (volume, proportion of patients who are children/youth, prior participation in the collaborative care program, public/private practice). We will try to recruit all 60 GPs currently in the program, but have powered the study for 45.

GPs will be approached by staff from the CMHC with whom they already interact regularly. If they are interested in the study, one of the Iranian investigators will contact them, provide more information and obtain written consent. GPs will receive a payment of about \$200 to cover the time that will be required for training in child/youth mental health skills. In addition, as in the current Tehran University Collaborative Care Program (TUCCP), they will receive a care coordination payment for patients identified as having a mental health problem who they successfully follow for at least three months (presently this applies only to adults – for participants in this trial it will apply children as well). Successful follow-up is defined as a) monthly visits with the GP for the first three months after treatment initiation or substantial change in treatment, and then b) follow-up visits at no more than 3-month intervals for patients who are stable. Patients for whom the GP is not certain of the diagnosis, or a) for whom there is concern for self-harm, harm to others, psychosis, mania, or a clinically important drop in function, or b) who cannot be stabilized after three months or may be having severe side effects to medications, are referred to the CMHC.

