### Data analysis approach

Analysis will follow a pre-determined plan and take place under the direction of the trial statistician. Analyses will be masked to study arm until data collection is finalized. Exploratory analyses will confirm expected distributions and the prevalence and patterns of missing data.

We will use appropriate methods for missing or censored data, such as multiple imputation or full information maximum likelihood [59].

The outcomes in each set of analyses will first be explored with simple bivariate statistics. Multilevel models with random effects will model patient outcomes, which are clustered within GPs [60]. The basic approach has the following form: if the study ultimately has  $I$  clusters ( $i=1:I$ ), 3 time points ( $j=1:3$ ), and  $N$  patients per cluster ( $k=1:N$ ), individual patient outcomes are modeled as  $Y_{ijk} = \mu_{ij} + \gamma C_{ijk} + e_{ijk}$  where  $e_{ijk}$  has a  $iid N(0, \sigma_e^2)$  distribution. Individual covariates included at this level (denoted by  $C$ ) will include child age, gender, and initial SDQ symptom and functioning scores. The mean outcome for cluster  $i$  at time  $j$  can be expressed as:  $\mu_{ij} = \mu + \alpha_i + \beta Z_{ij} + X_{ij}\theta$ , where  $\alpha_i$  is a random effect for the cluster and  $Z_{ij}$  are the cluster-level covariates (e.g., public or private GP practice, practice size, the three staggered training waves to which the GP belongs), and  $X_{ij} = 0$  if the cluster is a control practice or  $= 1$  if it is an intervention practice.

Interaction terms between intervention status and a hypothesized cluster-level moderator (e.g. GP's public or private practice, practice size, training wave) will be used for exploratory analyses of effect heterogeneity.

Analysis will be by intent-to-treat based on the intervention status of the GP. However, intent-to-treat analysis does not take into account the level of intervention actually received by individual patients. Therefore, the intent-to-treat data will be presented along with data describing, for each arm: 1) the proportion of patients receiving any form of collaborative mental health treatment, 2) the proportion of patients who do receive mental health treatment who receive it solely from a CMHC; and 3) the proportion of patients whose GP left the collaborative during the course of the study. Only (3) will be considered a protocol deviation, since per the

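### The sample size of 135 per arm is for the mean of the 3- and 6-month scores, but the effect is defined at the final assessment, where the stated change-score test has about 72% power

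*Protocol*

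**What the plan says.** In the Protocol, Population and recruiting, item 1 (children/youth and their parents), the calculation uses the *change* option of a Stata routine, described as a t test comparing the arms on outcome minus baseline. The effect is tied to one visit: "We estimated that the difference in change scores at the final assessment would be about 2.5 points on the SDQ total difficulties scale". The spread is given as "An estimated standard deviation of 7.2 was also drawn from these sources (thus an estimated effect size of .34" (2.5/7.2 is 0.347). On the variance the text says "The variance is adjusted for correlations between the outcome measures and between the outcome and baseline measures", and gives the values: "Correlations between baseline and outcome measures and between outcome measures were estimated at .37 and .55, respectively". With alpha 0.05 and power 0.8, "these parameters yielded a sample size of 135 per study arm (270 total").

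The next steps build on that figure. A design effect of 1.05 gives about 284 at outcome. Then "Assuming a worst-case of 20% loss of patients to follow-up would require enrolling 355 patients", and a 24% screen-positive rate gives about 1479 to be screened. Follow-up calls are at 3 and 6 months, and the 6-month call is the final one.

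The Data analysis approach section plans something else: a multilevel model over three time points, with patients clustered in GPs. Its individual covariates "will include child age, gender, and initial SDQ symptom and functioning scores". It has one intervention term, set to 0 or 1 by practice, with no visit-specific effect.

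**The concern.** A correlation between outcome measures enters this variance formula only when more than one follow-up score is averaged. A contrast at the final assessment has a single follow-up score, so the .55 should play no part in it. Averaging two imperfectly correlated scores lowers the variance, and therefore the required sample size. The text thus takes its effect from one visit and its variance from the mean of two.

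What is at stake is the meaning of the 80% claim. Readers will use it to judge a null SDQ result. As written, it does not apply to the contrast it names, and the text does not say that the powered contrast is an average or why 2.5 points should hold as one.

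**Working it through.** **Inputs.** Difference 2.5, SD 7.2, baseline-outcome correlation .37, outcome-outcome correlation .55, alpha 0.05, power 0.8, 45 GPs, design effect 1.05, 20% loss and 24% screen-positive are all from Population and recruiting. A two-sided test is my assumption, since sidedness is not stated.

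**Formula.** n per arm = 2(1.96 + 0.8416)² × (7.2/2.5)² × factor = 130.2 × factor. With *m* follow-up scores averaged, the factor for a change score is (1 + (m − 1) × .55)/m + 1 − 2 × .37.

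**Reproducing the plan (m = 2).** Factor = 1.55/2 + 1 − 0.74 = 1.035, so n = 134.8, i.e. 135 per arm. Then 270 × 1.05 = 283.5 (about 284), 284/0.8 = 355 and 355/0.24 = 1479. Every figure in the protocol is recovered.

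**The contrast as worded (m = 1).** Factor = 1 + 1 − 0.74 = 1.26, so n = 164.06, i.e. 165 per arm. Carried forward: 330 × 1.05 = 346.5 (347 analysed), 347/0.8 = 434 enrolled, and 434/0.24 = about 1,808 screened.

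**Power with the planned numbers.** The effective size is 284/1.05/2 = 135.2 per arm. The SD of the 6-month change is 7.2 × √1.26 = 8.08. The standard error of the difference is 8.08 × √(2/135.2) = 0.983, and 2.5/0.983 = 2.54. Power is Φ(2.54 − 1.96) = 72%, or 70% from a t distribution on 43 df (45 GPs minus 2).

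**Other readings of the inputs.** Taking 7.2 as the SD of the change score itself gives 131 per arm, not 135, and ignores both correlations. A one-sided test at one visit gives 130. It reaches 135 only if the rounded effect size .34 is used, and then .55 goes unused. Using .55 as the baseline correlation at one visit gives 118. Only the two-visit average uses every stated input and returns 135 exactly.

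**If the average is the target.** The change-score calculation then needs a mean difference of 2.5 over both visits. If the 3-month difference were 2.0 (assumed), the average is 2.25 and power at 135 per arm is 71%. If it were 1.25 (assumed), the average is 1.875 and power is 56%.

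**The baseline-adjusted analysis.** Here the two follow-ups are outcomes and baseline SDQ is a covariate, which is how I read the model, with .37 assumed at both visits.

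| Contrast | Factor | n per arm for 80% | Power with 284 analysed |
|---|---|---|---|
| 6 months alone | 1 − .37² = 0.863 | 113 | 87% (85% on 43 df) |
| 3/6-month average, effect 2.5 | .775 − .37² = 0.638 | 84 | 95% |
| 3/6-month average, effect 2.0 (assumed) | 0.638 | – | 82% |
| 3/6-month average, effect 1.875 (assumed) | 0.638 | – | 76% |

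**The case against.** The strongest reply is that nothing was miscalculated. The printed inputs give 135, 284, 355 and 1479, and by listing a correlation between outcome measures the text discloses that both follow-ups entered the variance. That stands: the fault is a mismatch between the named time point and the variance used. It does not remove the mismatch, because the text supports 2.5 points only at the last visit and never calls the target an average.

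A second reply is that 72% belongs to a test the protocol does not plan to run. The model has one intervention effect not tied to a visit, so a calculation that pools visits is closer to it than a 6-month-only one. At an equal effect, using change scores instead of baseline adjustment is conservative on the protocol's own correlations. This also stands, and it limits the consequence.

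A reader might infer from the 72% that the trial is too small, or that 355 enrolled and 1479 screened must rise to 434 and about 1,808. The documents do not support that. The larger numbers apply only if the 6-month change-score test is the analysis, and the Data analysis approach section plans baseline adjustment.

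**Conclusion.** The stated 80% is wrong for the contrast the protocol names. For a change-score t test at the final assessment, the planned enrolment gives about 72% (70% on 43 df), and 80% would need 165 per arm. The 135 per arm is correct only for the mean of the two follow-ups, with 2.5 points as the average difference.

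This is an inconsistency in the power statement and does not show a shortfall in the planned analysis. With baseline adjustment the same enrolment gives about 87% at 6 months. For the average it gives about 95% if 2.5 holds on average, falling to 82% at 2.0 and 76% at 1.875. These figures rest on the protocol's SD, correlations, ICC of .01 and 20% loss, all taken as given, and on a two-sided test. The two smaller average effects are illustrations, not figures from the protocol.

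**What to change.** Name one target contrast, either the SDQ difference at 6 months or the mean difference over 3 and 6 months. Use it in both the sample-size text and the Data analysis approach model, and restate the power for the baseline-adjusted analysis of that contrast.

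- If the target is 6 months, state about 87% (85% on 43 df) with 355 enrolled, and make the intervention effect in the model specific to that visit. Changing the sample-size text alone would leave it at odds with the model, which does not single out a visit.
- If the target is the 3/6-month average, say so, and either justify 2.5 points as an average effect or show the power for a smaller one.
- If the change-score test at 6 months is kept, state about 72% (70% on 43 df).

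The cost is rewording the sample-size paragraph and, for a 6-month target, the model description. Enrolment, screening and data collection do not change.
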